#### Intervention

Three sessions will be used for both pricking the blood at ExHN 9 and acupuncture treatment at LI 20. The sessions will be administered over a period of 3 weeks (one session per week). Certified acupuncture practitioners who have a minimum of 3 years of clinical experience obtained after a 6-year oriental medical college course will perform the acupuncture treatment. The practitioners will take a one-day training course for this trial. This course will include the study protocol, methods for acupuncture treatment, and basic information on clinical research.

#### Pricking blood at ExHN 9

Three sessions of pricking blood at ExHN will be performed once per week for 3 weeks in patients assigned to the experimental group. Patients that will receive acupuncture treatment will be pricked on the intranasal membrane at bilateral ExHN 9, which is located at the junction between the mucosa of the alar cartilage of the nose and the nasal concha in the nostril. This point will be treated with 0.30 × 120 mm disposable acupuncture needles (Dongbang Co., Korea) according to 'WHO Standard Acupuncture Point Locations' in the Western Pacific Region [17].

#### Acupuncture treatment at LI 20

Three sessions of acupuncture treatment at LI 20 will be performed once per week for 3 weeks in patients assigned to the control group. Patients will receive acupuncture treatment at bilateral LI 20. For bilateral LI 20, needles will be inserted obliquely toward their ipsilateral nostrils to a depth of 0.3 cm. This point will be treated with 0.30 × 40 mm disposable acupuncture needles (Dongbang Co., Korea) according to 'WHO Standard Acupuncture Point Locations' in the Western Pacific Region [17]. Patients will remain in the supine position for 15 min during acupuncture treatment.

### Outcome measures

#### Primary outcome

Primary outcomes will be presented by mean change in total nasal symptom score (TNSS) from baseline to the end of the trial. TNSS is a scoring system that consisted of rhinorrhea, sneezing, nasal itching, and nasal obstruction, which are scored on a severity scale from 0 to 3 (0 = none, 1 = mild, 2 = moderate, and 3 = severe). The TNSS is calculated by summation of all four symptom scores [5,7]. For each visit at baseline and the end of trial, the patient will record his nasal symptoms using the TNSS scoring system.

#### Secondary outcomes

Secondary outcomes will be evaluated using the Mini-Rhinoconjunctivitis Quality-of-Life Questionnaire (MiniRQLQ).

#### MiniRQLQ

The MiniRQLQ consists of five domains with a total of 14 questions: two questions for practical problems, and three questions each for activity limitations, nose, eye, and other symptoms [18]. The MiniRQLQ is a self-administered scoring system. The patients will mark one of the seven Likert-like scales (0 = no impairment to 6 = maximum impairment) for each of the 14 questions.

### Statistical methods

#### Statistical analysis plan

Statistical analysis will be conducted on an intention-to-treat basis with a 95% confidence interval using SPSS version 12.0 for Windows. Missing values for patients that drop out of the study will be analyzed using the last observation carried forward (LOCF) method. Data will be displayed as the mean ± standard deviation (SD) for continuous data or *n *(%) for categorical data. To control for baseline differences between groups, variables that are significantly different at baseline will serve as covariates in the analyses.

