#### Randomization and blinding

After enrollment, participants will be randomly assigned to control and experimental groups. The allocation ratio will be 1:1. Randomization will be performed at a site remote from trial location. Random numbers will be generated using a computerized random-number generator through the block-randomization method (Excel, Microsoft Office 2007) for sequence generation. Two separate databases will be generated: a 'patient' database, which lists basic information, such as the patient name, contact details, and so on, and a 'randomization' database, which contained data on patients that have been registered in the trial along with their allocations. The 'patients' database will be accessible to any researcher whereas the 'randomization' database will be password-protected so that it will be accessible only by the principal investigator and a nominated statistician [16]. The assessor, who will not be the acupuncture practitioner, and who will be blinded to the allocation results until the end of study, will assess the outcome of treatment.

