#### Demographic and clinical characteristics

Demographic and clinical characteristics of participants in the control and experimental group will be compared upon admission using an independent sample *T*-test (continuous data) and chi-square analysis (categorical data).

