#### Efficacy analysis

The statistical calculation for the paired sample *T*-test or independent sample *T*-test will be done for the mean change of TNSS and miniRQLQ score in comparison between and within groups from baseline to the end of trial. Non-parametric methods will be used when assumptions of normality are violated.

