#### Sample size

This study is a pilot study to evaluate the clinical effects of pricking blood at ExHN 9 on NAR. Because this trial will be designed for a short duration, lasting 3 weeks, with the intention of decreasing the drop-out rate, the desired sample size for this pilot study is 50 patients, with 25 for each group, assuming a drop-out rate of 20%.

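### Baseline significance tests decide whether baseline TNSS is adjusted for, so it rarely is: the change-score comparison keeps regression-to-the-mean bias and loses precision, without inflating overall type I error

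*Protocol article*

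**What the plan says.** The article's *Statistical analysis plan* section sets a rule for covariates: "variables that are significantly different at baseline will serve as covariates in the analyses". The section *Demographic and clinical characteristics* supplies the screening step: "Demographic and clinical characteristics of participants in the control and experimental group will be compared upon admission", by independent t-test for continuous data and chi-square for categorical data.

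The primary outcome is the mean change in TNSS from baseline to the end of the trial. The *Efficacy analysis* section compares mean change in TNSS and MiniRQLQ by t-tests, paired or independent, and adds: "Non-parametric methods will be used when assumptions of normality are violated". No section names baseline TNSS, or any other variable, as a covariate that is always included.

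On design, *Randomization and blinding* states "The allocation ratio will be 1:1", and *Sample size* states "the desired sample size for this pilot study is 50 patients, with 25 for each group", with 20% drop-out assumed. No significance level is given; the nearest statement is "intention-to-treat basis with a 95% confidence interval".

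**The concern.** Under proper randomisation, a baseline test examines a null hypothesis already known to be true. It flags each variable about 5% of the time by chance, however strongly or weakly that variable predicts outcome. Baseline TNSS is the obvious predictor of end-of-trial TNSS, yet under this rule it enters the model only when chance makes it significant.

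When it does not enter, the analysis is the difference in mean change. A change score fixes the slope on baseline at 1, whereas the slope in the data will usually be smaller. The arm that starts with worse symptoms is then expected to improve more through regression to the mean, and the comparison flatters it. Fixing the slope at 1 also costs precision. Both matter in a trial of 50 patients, where chance imbalances are comparatively large and where, according to the *Discussion*, positive results would lead to a large trial.

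**Working it through.** **Inputs from the article.** 25 per arm, 1:1 allocation, t-test screening at baseline, primary outcome of change in TNSS. The sample size cannot be reproduced, because no effect size, SD or power is given. Only the drop-out arithmetic can be checked, and it is consistent: 20 / (1 − 0.20) = 25 per arm.

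**Assumptions.** Two-sided 5% level, inferred from the 95% interval; equal SDs at baseline and end of trial; baseline-to-end correlation rho of 0.3, 0.5 or 0.7. The article gives no rho. Units are SDs of TNSS.

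**1. Imbalance that triggers adjustment.** The smallest significant baseline difference is t(0.975, 48) × √(2/25) = 2.011 × 0.283 = 0.569 SD. With 20 per arm it would be 0.640, but the screening is done on admission, so 25 applies. In simulation (40,000 trials per setting) baseline TNSS was flagged in 4.9% to 5.1% of trials.

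**2. Bias left in the change score.** Given a baseline imbalance D, the expected end-of-trial difference under no effect is rho × D, so the expected difference in change is rho × D − D = −(1 − rho) × D. The typical imbalance is the mean absolute value, √(2/π) × √(2/25) = 0.798 × 0.283 = 0.226 SD.

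| rho | Size of bias at D = 0.569 | Size of bias at D = 0.226 |
|---|---|---|
| 0.3 | 0.40 SD | 0.16 SD |
| 0.5 | 0.28 SD | 0.11 SD |
| 0.7 | 0.17 SD | 0.07 SD |

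**3. Precision.** In units of SD² per patient, the change-score variance is 2(1 − rho) and the ANCOVA variance is 1 − rho². The ratio is (1 − rho²) / [2(1 − rho)] = (1 + rho)/2, or 0.65, 0.75 and 0.85. For equal precision the change score needs 1/ratio − 1 = 54%, 33% and 18% more patients. Estimating the slope in a trial this small trims the gain: simulated ratios are about 0.66, 0.76 and 0.87, or about 51%, 31% and 15%.

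**4. How much of the gain the plan's rule keeps.** The simulation had baseline TNSS as the only candidate covariate. The SD of the treatment estimate was:

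| rho | Change score | Plan's rule | Fixed ANCOVA | Share of variance gain kept by the rule |
|---|---|---|---|---|
| 0.3 | 0.3328 | 0.3173 | 0.2720 | (0.1108 − 0.1007) / (0.1108 − 0.0740) = 27% |
| 0.5 | 0.2832 | 0.2738 | 0.2475 | (0.0802 − 0.0750) / (0.0802 − 0.0613) = 28% |
| 0.7 | 0.2182 | 0.2142 | 0.2029 | (0.0476 − 0.0459) / (0.0476 − 0.0412) = 27% |

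The rule keeps about a quarter of the variance gain, because it adjusts only in the extreme trials. It keeps little of the power gain, because the t-test used in the other 95% still carries the larger standard error. At an assumed true effect of 0.8 SD, power was:

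| rho | Change score | Plan's rule | Fixed ANCOVA |
|---|---|---|---|
| 0.3 | 65% | 66% | 82% |
| 0.5 | 79% | 80% | 89% |
| 0.7 | 95% | 95% | 97% |

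**5. Type I error.** Overall, the rule rejected a true null in 4.0%, 4.3% and 4.4% of simulated trials. A second simulation of 60,000 trials gave 4.0%, 4.4% and 4.6%. At the typical imbalance the conditional rate was 3.6%, 3.9% and 4.5%. Only just below the 0.569 SD threshold does it reach about 17%, 13.5% and 10% (normal approximation).

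**The case against.** **Error rates.** A reader might infer from the 10% to 17% figures that the plan inflates false positives. It does not. Those rates belong to the edge of the unadjusted range, an imbalance that about 5% of randomised trials reach or exceed. Averaged over trials, the covariate rule is slightly conservative. No figure here covers the non-parametric switch, so no claim is made about its effect on error.

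**Imbalance left uncorrected.** A reader might also say that TNSS imbalances up to 0.57 SD go uncorrected. For TNSS that is wrong, because the outcome is change and baseline is already subtracted. What remains is over-correction by (1 − rho) times the imbalance. Only for other, unflagged prognostic variables is the imbalance left unadjusted.

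**Unspecified analysis.** It is tempting to say that the primary analysis is not fixed until the data are seen. The article does state its triggers in advance, and a covariate model is implied once a variable is flagged. That the model is not named, although a t-test cannot carry covariates, is detail a condensed article may leave to the full plan. The branching is poor practice, but not an absence of a plan.

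**Pilot status.** The article says that the trial is small and cannot be conclusive. That limits the consequences. It does not favour the rule, since small samples are where chance imbalance is largest and precision scarcest.

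What stands after these objections is that the article states the covariate rule outright, so it cannot be excused as detail left to another document, and that it performs worse than fixed adjustment at every correlation examined.

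**Conclusion.** The point holds as one of conditional bias and lost efficiency. The rule leaves baseline TNSS out of the model in about 95% of trials. In those trials the change-score comparison is biased by about 0.07 to 0.16 SD at a typical imbalance, and by at most 0.17 to 0.40 SD, towards the arm that starts worse. Fixed ANCOVA would reduce the change-score variance by roughly 15% to 35%; the plan's rule keeps about a quarter of that reduction and adds about one percentage point of power or less.

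The 0.57 SD threshold depends on the inferred two-sided 5% level. The other sizes depend also on the assumed correlations and equal SDs. The direction does not depend on the particular correlation: with equal SDs, ANCOVA has the smaller large-sample variance for any rho below 1. This should be changed, but it does not invalidate the trial.

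**What to change.** Replace the covariate sentence in *Statistical analysis plan* with wording such as:

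> The primary analysis is an ANCOVA of end-of-trial TNSS on treatment group with baseline TNSS as covariate, whatever the observed baseline balance, reported as the adjusted mean difference with its 95% confidence interval. MiniRQLQ is analysed in the same way with baseline MiniRQLQ as covariate. Baseline significance tests are not used to select covariates.

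The between-group t-test in *Efficacy analysis* should be brought into line. The primary outcome need not be redefined: regressing change in TNSS on treatment and baseline TNSS gives the same treatment difference as regressing the end-of-trial score.

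The cost is protocol wording and one degree of freedom. Baseline TNSS and MiniRQLQ are already collected, and the trial status is given as not yet recruiting, so the change can be made before any data exist.

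Two further changes are optional: dropping the baseline tests from the descriptive comparison, and replacing the non-parametric switch with a bootstrap or permutation check on the ANCOVA estimate.

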#### Demographic and clinical characteristics

Demographic and clinical characteristics of participants in the control and experimental group will be compared upon admission using an independent sample *T*-test (continuous data) and chi-square analysis (categorical data).

#### Efficacy analysis

The statistical calculation for the paired sample *T*-test or independent sample *T*-test will be done for the mean change of TNSS and miniRQLQ score in comparison between and within groups from baseline to the end of trial. Non-parametric methods will be used when assumptions of normality are violated.

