## Method/Design

### Objective

The current randomized, assessor single-blinded, parallel-group, single-center study was designed to evaluate the clinical efficacy of pricking blood at ExHN 9 for the treatment of NAR relative to the control group, which involved administration of acupuncture treatment at LI 20.

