This study will be the first randomized trial to evaluate the efficacy of pricking blood at ExHN 9 for the treatment of NAR. The main focus of this study is to investigate the effectiveness of pricking blood at ExHN 9 in decreasing the TNSS, as a primary outcome, relative to acupuncture treatment at LI 20, which is commonly used in clinical practice and has been shown to be effective in treating patients with chronic rhinitis including NAR. This trial will provide information needed to answer relevant clinical questions regarding the efficacy of pricking blood at ExHN 9 for the treatment of NAR. Although the size of this trial is small and cannot provide conclusive results on the effectiveness of pricking blood at ExHN 9, if positive results are obtained, a large clinical trial will be conducted in the future.

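### Within-group paired t-tests are listed as efficacy analyses beside the between-group test, and nothing says that the between-group comparison decides

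*Protocol article*

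**What the plan says.** The aim is comparative. The Objective evaluates pricking at ExHN 9 "for the treatment of NAR relative to the control group", and the Discussion puts the main focus on its effectiveness "in decreasing the TNSS, as a primary outcome, relative to acupuncture treatment at LI 20".

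The analysis text is broader. Efficacy analysis gives its scope as the "mean change of TNSS and miniRQLQ score in comparison between and within groups from baseline to the end of trial". Two tests are named to cover that scope, in the statement that a "paired sample *T*-test or independent sample *T*-test will be done". No order of importance is given, and the within-group results are not called descriptive. The Primary outcome section does not settle it: "Primary outcomes will be presented by mean change in total nasal symptom score (TNSS) from baseline to the end of the trial" describes a change over time and names no contrast between arms.

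The Discussion then says that "if positive results are obtained, a large clinical trial will be conducted in the future", without saying on which comparison a result would count as positive.

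**The concern.** A paired test within one arm is an uncontrolled before-after comparison. It makes no use of the randomised control and cannot answer a question about ExHN 9 relative to LI 20. Placed under efficacy with no ranking, it offers a second route to a favourable reading.

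The design makes that route easy to take. There is no sham or untreated arm, patients record the TNSS themselves, and only the assessor is described as blinded. The Discussion itself accepts that placebo interventions can influence patient-reported outcomes, and the Background says that symptoms may be intermittent or seasonal. Some improvement in both arms is therefore plausible whether or not the treatments differ. A significant paired result for ExHN 9 beside a non-significant one for LI 20 could then be read as a difference between treatments, and could support the decision to run a large trial.

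**Working it through.** **The plan's own figure.** The only design number is the sample size: "the desired sample size for this pilot study is 50 patients, with 25 for each group", allowing 20% drop-out. The article states no effect size, SD or power, so no power formula can be reproduced. The drop-out step is consistent with 20 completers per arm: 20 / (1 − 0.20) = 25 per arm, and 40 / (1 − 0.20) = 50 in total. The 20 and 40 are inferred, not stated.

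**Inputs.**
- n = 25 per arm (Sample size), with n = 20 as the figure after 20% drop-out.
- Two-sided 5% level. This is assumed from the "intention-to-treat basis with a 95% confidence interval", since no significance level is stated.
- True difference between treatments: zero.
- Common improvement δ in both arms, in SDs of change: 0.3 to 0.8. This is an assumption, because the article gives no SD or expected change. If the SD of change were 2.5 points, also an assumption, the range would be 0.3 × 2.5 = 0.75 to 0.8 × 2.5 = 2.0 points on a scale of 0 to 4 × 3 = 12.

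**Formulas.**
- Chance p that one arm's paired test shows significant improvement: p = P(T > t(0.975, n − 1)), where T is noncentral t with n − 1 degrees of freedom and noncentrality δ√n.
- The arms are independent and improve equally. So the chance that ExHN 9 is significant and LI 20 is not is p(1 − p), and the chance that both are significant is p².
- The rejection rate of the independent-sample t-test on change was simulated, with 50,000 trials per setting.

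**Results, 25 per arm.**

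| δ (SD of change) | ExHN 9 paired test significant, p | ExHN 9 only, p(1 − p) | Both arms, p² | Between-group test significant |
|---|---|---|---|---|
| 0.3 | 30.2% | 21.1% | 9.1% | 5.0% |
| 0.4 | 48.4% | 25.0% | 23.4% | not simulated |
| 0.5 | 67.0% | 22.1% | 44.9% | 4.9% |
| 0.6 | 82.1% | 14.7% | 67.4% | not simulated |
| 0.8 | 97.0% | 2.9% | 94.1% | 5.1% |

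For example, at δ = 0.5 the noncentrality is 0.5 × √25 = 2.5, p = 0.670, and p(1 − p) = 0.670 × 0.330 = 0.221.

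**Results, 20 per arm.** At δ = 0.3, 0.5 and 0.8, p is 24.6%, 56.4% and 92.4%, and ExHN 9 alone is significant in 18.6%, 24.6% and 7.0%. The between-group test rejects in 5.2%, 5.0% and 4.9%.

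The between-group rate does not depend on how much both arms improve. About half of it, 2.5%, favours ExHN 9, and that is the fair comparator for the ExHN 9-only column. At δ = 0.8 that column (2.9%) is close to it. At that end of the range the usual misleading pattern is significance in both arms.

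**The case against.** The strongest defence is that the intended contrast is clear from the rest of the article. The Objective and the Discussion both speak of ExHN 9 relative to LI 20, and the Discussion does so in the same sentence as the primary outcome. Covariate adjustment for baseline differences between groups only makes sense for a between-group analysis. The trial is called a pilot and concedes that it cannot be conclusive, and within-group p-values do not change the error rate of the between-group test. All of this is true. It shows what the authors intend, but it does not rank the tests listed under efficacy or define the outcome that would lead to a large trial.

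Four stronger readings are tempting, and the document does not support them.
- A reader might infer from the word joining the two tests that a paired test could replace the between-group test. A paired test cannot compare independent arms, so the natural meaning is paired within arms and independent between them. Only the side-by-side use is explicit.
- A reader might infer a success rule that a significant paired test would satisfy. The article has no formal success rule.
- A reader might take the chance that exactly one arm is significant, 2p(1 − p), as the risk of a false claim for ExHN 9. At δ = 0.4 and 0.6 this is 50% and 29%, but half of those trials favour LI 20, leaving 25% and 15%. Significance in both arms would not suggest superiority over LI 20 either.
- A reader might infer that regression to the mean is built in. Eligibility sets no minimum TNSS, so its size is unknown. The calculation needs only some equal improvement, whatever its cause.

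**Conclusion.** The concern holds as a mismatch between the aim and the analysis text. Within-group tests stand as efficacy analyses with no ranking, for a question that only the between-group comparison answers, and the outcome that would justify a large trial is left undefined. Because the article affirmatively lists these tests under efficacy, this is more than detail left to an unseen analysis plan.

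The percentages rest on equal improvement in both arms, approximately normal changes, two-sided 5% testing and an assumed δ. They show how weakly a paired result bears on the question and do not forecast this trial. The planned between-group test is not invalidated. The risk lies in how results are labelled and in what leads to the next trial.

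**What to change.** - **Efficacy analysis:** name the between-group difference in TNSS change from baseline to the end of the trial (ExHN 9 minus LI 20) with its 95% CI as the sole primary efficacy analysis, preferably adjusted for baseline TNSS. Treat MiniRQLQ in the same way as secondary. This keeps the stated endpoint. If the adjustment is adopted, the Statistical analysis plan section should fix baseline TNSS as a covariate in advance, whatever the baseline tests show.
- **Within-group changes:** report the mean change and CI in each arm as description, not as efficacy tests.
- **Discussion:** define a positive result by the between-group estimate and its CI.

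Recruitment has not begun according to Trial status, so no data are affected. The cost is a few sentences and the loss of within-group significance statements.
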